# Evaluating the effectiveness of telehealth-delivered Child and Family Traumatic Stress Intervention (CFTSI) for children and adolescents following recent trauma: a multi-site randomized controlled trial in France

**DOI:** 10.1186/s40359-025-03585-0

**Published:** 2025-11-12

**Keywords:** Post-traumatic stress, PTSD, Early intervention, Trauma, Family therapy

## Abstract

**Background:**

Children and adolescents exposed to traumatic events (TEs) are at risk of developing post-traumatic stress disorder (PTSD), with long-term emotional, cognitive, and social consequences. Early interventions within the first months post-trauma are essential, yet structured, evidence-based approaches remain limited. The Child and Family Traumatic Stress Intervention (CFTSI) is a brief, family-centered approach that enhances parental support and reduces post-traumatic symptoms. While effective in the U.S., its implementation in European settings, particularly via telehealth, remains unexplored.

**Objective:**

This study evaluates the effectiveness of telehealth-delivered CFTSI in reducing post-traumatic symptoms in children aged 7–17 after recent TEs, compared to non-specific psychological support. Secondary objectives include assessing symptom persistence at three months, parental PTSD symptoms, and predictors of treatment response.

**Methods:**

This study is a multicenter, evaluator-blinded RCT comparing CFTSI to supportive counseling. Eligible children (aged 7–17) must have experienced a TE within the past 45 days and exhibit at least one posttraumatic stress symptom. Exclusion criteria include severe cognitive impairment, ongoing abuse, or acute psychiatric emergencies.The CFTSI group will receive 5–8 structured, family-focused telehealth sessions targeting parent-child communication and coping. The control group will receive supportive counseling. The primary outcome is post-traumatic symptom reduction, assessed using the Child Posttraumatic Stress Checklist 3 months after completion of the program. Secondary outcomes include three-month symptom persistence, parental PTSD symptoms, and predictors of response. Analyses will use ANCOVA and regression models adjusted for baseline characteristics.

**Discussion:**

This is the first RCT in France evaluating telehealth-delivered CFTSI. Conducted across four sites, findings will inform trauma care integration at regional and national levels. By improving accessibility and supporting trauma-exposed families, this study aims to enhance clinical training and advance evidence-based early interventions.

**Trial registration:**

Clinicaltrials.gov. Number NCT07031817. Registered on the 2nd of October, 2025.

## Background

Children and adolescents worldwide are exposed to alarmingly high rates of sexual abuse, physical assault, violent accidents, and other potentially traumatic events (TEs) [1–3], as defined by the DSM-5 criteria [4]. Childhood exposure to trauma is associated with an increased risk of mental health disorders, including post-traumatic stress disorder (PTSD), depression, anxiety, and substance use disorders, with potentially lasting effects on development and well-being [5, 6]. Traumatic experiences can also disrupt family dynamics, affecting not only children but also their parents, who may develop PTSD symptoms themselves [7].

Although some children experience spontaneous recovery following a single TE, PTSD remains prevalent, with 11% of children aged 5–18 years still meeting diagnostic criteria one year after the traumatic exposure [8]. PTSD in children and adolescents has well-documented negative effects on social, emotional, educational, and developmental outcomes [9]. While some individuals eventually recover, acute symptoms—such as intrusive thoughts, hyperarousal, irritability, fearfulness, sleep disturbances, and concentration difficulties—can cause significant distress for both the child and their family. These symptoms not only result in immediate suffering but also contribute to functional impairment and may hinder optimal development [10]. The persistence and severity of posttraumatic symptoms are influenced by multiple factors, including the type of TE, parental mental health, and the availability of family and social support [3].

Although multiple evidence-based treatments exist for PTSD in children [11], there is limited research on early interventions—those delivered within the first months of trauma exposure—to alleviate acute post-traumatic symptoms and strengthen family support, potentially playing a role in preventing chronic posttraumatic symptoms. The Child and Family Traumatic Stress Intervention (CFTSI) is a brief, evidence-based early intervention developed at the Yale Child Study Center for children aged 7–17 who have recently experienced a TE [12, 13]. This family-centered intervention consists of 5–8 structured sessions designed to enhance parental support, improve parent-child communication, and teach targeted coping strategies to reduce acute post-traumatic symptoms. CFTSI has been implemented in children exposed to various TEs, including sexual and physical abuse, domestic and community violence, road accidents, and injuries [13, 14]. A randomized control trial (RCT) by Berkowitz et al.. found that children receiving CFTSI had significantly fewer full and partial PTSD diagnoses at three months compared to a control group receiving psychoeducation and non-specific psychological support [13]. Additionally, a multicenter study involving 1,190 families demonstrated that CFTSI significantly reduced acute post-traumatic symptoms, regardless of age, gender, trauma type, or history of prior exposure [14]. A meta-analysis further supported its effectiveness, showing reductions in both child and parent PTSD symptoms, aligning with extensive literature on the impact of parental mental health on child recovery following trauma [15]. Parents experiencing distress or post-traumatic stress in response to their child’s trauma may struggle to provide emotional stability, thereby exacerbating the child’s difficulties [16]. Conversely, when parents receive adequate support and demonstrate effective coping strategies, children exhibit better adjustment, greater self-efficacy, and improved emotional regulation [3, 14]. Strengthening parental capacities after trauma is therefore essential for mitigating long-term consequences and fostering resilience. Additionally, recent research has also explored an online adaptation of CFTSI, demonstrating its feasibility and effectiveness in reducing PTSD symptoms in both children and parents, including those with repeated trauma exposure [17].

At the posttraumatic stress unit in the Child and Adolescent Psychiatry Department in the University Hospital of Montpellier (France), we have begun implementing CFTSI in routine clinical practice following training with the founders of the CFTSI. However, despite its demonstrated efficacy in the U.S., no RCTs have been conducted in France or other countries to evaluate CFTSI’s effectiveness in reducing acute symptoms in children and parents and its impact at three months post intervention. Moreover, a qualitative study exploring the experiences and perceived needs of parents of adolescents aged 11 to 17 who had been exposed to a TE within the past three months in Montpellier revealed that parents struggled to understand their children’s reactions, lacked explanations and knowledge about post-traumatic stress, and expressed feelings of failure and parental inefficacy in the face of their child’s suffering [7]. They were uncertain about the best approach to take in response to conflicting needs and tended to alternate between avoidant parenting strategies and coercive parental behaviors. This, in turn, affected their relationship with their child and led to conflictual dynamics [7]. These qualitative data highlight the need to provide parents with an early, adapted, and validated family intervention following their child’s traumatic exposure.

A family-centered approach such as CFTSI not only supports the child but also addresses parental distress, which is crucial for a stable recovery environment. The online format of CFTSI may enhance accessibility, reduce stigma, and expand the reach of trauma care. Given the lack of validated first-line early posttraumatic interventions for children and adolescents, testing CFTSI’s effectiveness over standard psychological support in a French population is a critical step towards integrating it as a standard care option at regional and national levels. Furthermore, a RCT involving the telehealth delivery of CFTSI may offer a practical, scalable solution to facilitate child and family recovery after traumatic exposure. This paper presents the study protocol for the RCT being conducted across four sites in France to examine the effectiveness of the CFTSI in reducing posttraumatic symptoms in children and their parents following the telehealth delivery of the intervention and at 3 months follow up.

## Methods

### Aims of the study

The primary aim of the RCT is to assess the effectiveness of the CFTSI in reducing post-traumatic symptoms measured by the validated French version of the Child Posttraumatic Stress Checklist [18] (CPC) at 3 months after completion of the program, in children and adolescents aged 7 to 17, exposed to a TE within the last 45 days, compared to standard child-centered psychological support.

The secondary aims of the study are the following:

• To examine the effectiveness of the CFTSI in reducing post-traumatic symptoms in children and adolescents on the CPC, at 3 months after completion of the program, compared to standard child-centered psychological support.• To examine the effectiveness of the CFTSI in reducing post-traumatic symptoms in parents on the validated French version of the Posttraumatic Stress Disorder Checklist for DSM-5 (PCL-5) [19], immediately after completion of the program and at three months follow-up, compared to standard child-centered psychological support.• To investigate factors associated with the child post-traumatic symptom scores on the CPC prior to any intervention (across all included participants):
◦ Gender, age, and socioeconomic status.◦ Prior traumatic exposures measured by the adapted French version of the CPC.◦ The presence of pre-existing psychiatric or neurodevelopmental disorders measured by the validated French version of the Schedule for Affective Disorders and Schizophrenia for school-age children, Kiddie-SADS, lifetime child and parent versions, K-SADS [20].◦ The presence of one or multiple traumatic exposures in the parent, assessed using the Life Event Checklist (LEC-5) [21].◦ A lower score on the resilience measurement scale assessing social and family support and the child’s skills: Child Youth Resilience Measure (CYRM), child version (one version for ages 7–10 and another for ages 11–17) [22, 23].◦ The severity of posttraumatic reactions among parents measured by the PCL-5.◦ The type of TE.• To investigate factors associated with changes in the CPC scores post-CFTSI:
◦ Gender, age, socioeconomic status.◦ Prior traumatic exposures measured by the adapted French version of the CPC.◦ The presence of pre-existing psychiatric or neurodevelopmental disorders measured by the K-SADS [20].◦ Changes in parent post-traumatic symptoms at the PCL-5 post CFTSI.◦ The presence of one or multiple traumatic exposures in the parent, assessed using the LEC-5 [21].◦ The type of TE.◦ The timing of the CFTSI delivery (for example, initiation of CFTSI within 60 days following the TE versus 30 days).◦ The evolution of the score on the resilience measurement scale assessing social and family support and the child’s skills: CYRM, child version (one version for ages 7–10 and another for ages 11–17) at baseline, immediately after completion of the program and at 3 months after the completion of the program [22, 23].•To examine the concordance between child and parent-reported post-traumatic symptoms by comparing the child version and the parent version of the CPC at baseline, immediately after completion of the program, and 3 months after completion of the program.• Examine the concordance between the perception of social support and the child’s skills as reported by the child and by the parents, at baseline, immediately after completion of the program, and 3 months after completion of the programby comparing the scores on the child and parent versions of the CYRM.

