## Participants

### Eligibility criteria

Families will be included if they meet the following inclusion criteria: (i) have a child or adolescent aged 7 to 17 years living in the family home, (ii) the child has been exposed to a TE aligning with the DSM-5 criteria for TEs within the past 45 days, (iii) there is at least one symptom on the Child Post-Traumatic Stress Checklist (CPC) at T0, (iv) at least one of the parents is available to participate in the intervention, (v) being fluent in French, both orally and in writing, and (vi) no concurrent participation in other therapeutic interventions aimed at treating traumatic stress symptoms during the inclusion period.

Participants will be excluded if they meet any of the following criteria: (i) parents and/or children present an imminent risk requiring immediate case management at the time of recruitment, or severe psychiatric disturbance or risks requiring specialist mental health services. This will be assessed by a clinical evaluation while gathering consent (preinclusion) and will be based on the clinical judgment; (ii) children are in foster care or in the process of being placed; (iii) there is suspicion of maltreatment or abuse perpetrated by one or both parents; (iv) children and/or parents have a known and/or documented intellectual disability, and (v) there is an absence of informed consent from at least one parent and/or refusal of participation by the child.

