#### Analysis of secondary endpoints

– Endpoints 1 (change in child CPC score between Baseline, immediately after completion of the program, and 3 months after completion of the program) and 2 (change in parent PCL-5 scores). The analysis will be carried out in the same way as for the primary endpoint.– Endpoints 3 (relationship between different participant characteristics and pre-intervention CPC score) and 4 (relationship between different participant characteristics and response to treatment).The factors associated with the CPC score will be analyzed using multiple linear regression. Determinants of response to treatment (change in CPC score) will also be analyzed using multiple regression.

– Endpoint 5 (concordance between child and parent CPC scores).The concordance between the CPC score obtained by the child and that obtained by the parents will be analyzed at each measurement time using the intraclass correlation coefficient (ICC) and its 95% confidence interval.

– Endpoint 6 (concordance between child and parent CYRM scores).The concordance between the CYRM score obtained by the child and that obtained by the parents will be analyzed at each measurement time using the intraclass correlation coefficient (ICC) and its 95% confidence interval.

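### The regression for change in CPC does not list the child's baseline CPC, so a factor related only to entry severity is liable to appear as a predictor of improvement

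*Protocol article*

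**What the plan says.** Under Aims of the study, the protocol article sets two related secondary aims.

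- The first is "To investigate factors associated with the child post-traumatic symptom scores on the CPC prior to any intervention (across all included participants"). It has seven factor bullets.
- The second is "To investigate factors associated with changes in the CPC scores post-CFTSI". It has eight factor bullets, beginning "Gender, age, socioeconomic status.◦ Prior traumatic exposures measured by the adapted French version of the CPC".

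Five bullets appear in both lists: gender, age and socioeconomic status; prior exposures; pre-existing disorder on the K-SADS; parental exposure on the LEC-5; and type of event. Two others reappear in altered form, as changes and not baseline values: "Changes in parent post-traumatic symptoms at the PCL-5 post CFTSI" and "The evolution of the score on the resilience measurement scale assessing social and family support". Timing of CFTSI is new. The child's T0 CPC score is not in the second list.

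Analysis of secondary endpoints (Endpoints 3 and 4) states: "Determinants of response to treatment (change in CPC score) will also be analyzed using multiple regression". No baseline CPC term is named. Eligibility sets a low entry threshold, "there is at least one symptom on the Child Post-Traumatic Stress Checklist (CPC) at T0", so entry scores can vary widely.

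**The concern.** T0 CPC is part of the outcome, because change is follow-up minus T0. Children who enter with higher scores have more room to fall, and regression to the mean works in the same direction. A factor that goes with a higher entry score will therefore tend to go with a larger drop, even if it has no bearing on recovery among children of equal entry severity.

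Endpoint 3 looks for factors related to T0 CPC, and Endpoint 4 then tests most of the same factors against change without holding T0 CPC fixed. Type of event or prior exposure, for example, could be reported as predicting a better response when it only marks children who started higher. Predictors of response are a stated objective of the trial, so a false lead here would misinform readers about whom CFTSI helps.

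**Working it through.** **Inputs from the protocol article.** Sample size: effect size 0.53, 80% power, two-sided 5%, 57 per group; with about 20% drop-out, 70 per group and 140 in total. Handling of missing data: two-sided tests at 5%.

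**The plan's own figure.** The two-sample t-test solution for 0.53 is 56.86, so 57 per group, as stated. Endpoint 4 has no sample size of its own. After 20% loss, 70 × 0.8 = 56 children remain in the CFTSI arm, which is the natural sample for factors of change after CFTSI. If both arms were used it would be 140 × 0.8 = 112.

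**Assumptions (not in the documents).** Unit variances at T0 and T1; factor-T0 correlation r; pre-post correlation p; one factor tested alone.

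**Case A: the factor acts only through T0.** Let T0 = rX + noise, T1 = pT0 + noise, change = T1 − T0. Then

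corr(X, change) = −(1 − p)r / √[(1 − p)² + 1 − p²].

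At p = 0.5 and r = 0.3: −0.15 / √(0.25 + 0.75) = −0.15. The t-test of this correlation gives the following rejection rates; simulations agree to within about 2 percentage points.

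| p | r | n = 56 | n = 112 |
|---|---|---|---|
| 0.5 | 0.2 | 11% | 18% |
| 0.5 | 0.3 | 20% | 35% (simulations 34-36%) |
| 0.5 | 0.4 | 31-32% | 56-57% |
| 0.3 | 0.3 | 26% | 47% |
| 0.7 | 0.3 | 13% | 23% |

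With T0 CPC in the model, the rate returns to about 5%.

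A second set-up used a balanced binary factor that raises T0 by b SD. Its spurious effect on improvement is b(1 − p) SD; for example, 0.5 × (1 − 0.5) = 0.25 SD. For b from 0.3 to 0.8 and p from 0.7 down to 0, the unadjusted model rejects in 8-53% of runs at n = 56. Adding T0 brings this back to about 5%.

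**Case B: the factor shifts T0 and T1 equally.** The factor is then unrelated to change, and the unadjusted model holds about 5%. In the T0-adjusted model the partial correlation is

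(1 − p)r / √[(1 − p²)(1 − r²)].

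At p = 0.5 and r = 0.3: 0.15 / √(0.75 × 0.91) = 0.18. The adjusted model rejects in 26-28% at n = 56 and 47-49% at n = 112, in the direction of poorer response.

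The factors are not randomised, and the documents contain nothing that decides between A and B for any of them.

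**The case against.** **Deferred detail.** The aims list factors of interest and do not specify a model. The protocol leaves the detail of the analyses to an SAP that is not shown, and the abstract says that the regression models adjust for baseline characteristics. This stands in part: nothing in the document excludes T0 CPC. But the protocol is not silent on this analysis. It enumerates the factors, down to example timing windows and the age versions of the CYRM, and an SAP that followed the list would carry the omission forward. The abstract does not name the characteristics. The rule under Demographic and baseline characteristics is triggered by imbalance between arms, which does not address a predictor analysis.

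**Raw change is a legitimate target.** The aim asks what is associated with change, and unadjusted change answers that. Adjusting for T0 is right under case A but creates its own false associations under case B. This stands in full, and it is why a single mandatory adjusted model would be the wrong remedy.

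**Stronger readings that a reader might infer.**

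- That any factor raising the entry score will be reported as a predictor. With 56 children, a Case A factor at r = 0.3 and p = 0.5 is falsely declared about one time in five, so usually it would not be. The rate also falls as the pre-post correlation rises.
- That Endpoint 4 merely repeats Endpoint 3 with the sign reversed. A correlation of 0.3 with T0 becomes −0.15 with change, and three of the eight bullets differ.
- That a child admitted with one symptom can improve by at most 4 points. The protocol does not say what item score counts as a symptom, so other items could be above zero.

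**Conclusion.** The concern holds as a liability to misattribution. The list of factors for change in CPC and the Endpoint 4 regression omit the child's T0 CPC, while five of the eight bullets are also tested as predictors of T0 CPC. Nothing elsewhere in the document requires the adjustment.

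For a factor acting only through T0, at assumed r = 0.3 and p = 0.5, the false-positive rate is about 20% (n = 56) or 34-36% (n = 112), against 5%. Over r from 0.2 to 0.4 it is about 11-32% and 18-57%. These figures rest on assumed correlations and on one factor tested alone, whereas the plan specifies multiple regression; they show the order of the problem and are not a forecast. The documents do not support treating the adjusted model as the only correct one.

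The point is worth correcting but of limited reach: it concerns one secondary, associational analysis and leaves the primary comparison untouched.

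**What to change.** In the secondary aim and in the Endpoint 4 analysis:

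1. Add the child's T0 CPC (child version) to the listed factors and report baseline severity as a predictor in its own right.
2. Report each factor's coefficient from the T0-adjusted model beside its coefficient from the unadjusted change model.
3. State that the first describes change at a given entry severity and the second raw change, and that the adjusted model can itself show a spurious association if a factor shifts T0 and T1 equally.
4. State that a factor whose result differs between the two models will not be presented as a determinant of response.

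The cost is one degree of freedom, one extra model and a few sentences. The score is already scheduled at T0 in Table 1, and the SAP need only be final before the last inclusion, so there is time to make the change.

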### Trial design

The study is a single-blind effectiveness multi-site superiority RCT, comparing the telehealth delivery of the CFTSI to the online delivery of child-centred psychological support with two parallel arms and blinded assessments of the outcome measures. Outcomes on child and caregiver measures will be assessed at baseline (T0), immediately after completion of the program (T1), and 3 months after completion of the program (T2). The primary outcome point is set as T1. The Standard Protocol Items: Recommendations for Interventional Trials (SPIRIT) [24] is outlined in Table 1.

**Table 1 Tab1:** Schedule of enrollment, interventions and assesments of primary and secondary endpoints; V = visit; T = time

Visit (V)	Pre-inclusion V0 Screening T −1 to 2 weeks	Inclusion V V1 Baseline T0	Psychological Intervention 1 + 5 weeks (1 session/week for 5 weeks) ± 1 to 3 additional sessions as needed over three weeks (2 months)	Follow-up V V2 T1(immediately after completion of the program ± 7 days)	Follow-up V V3 T2 days (3 months after completion of the programs ± 7 days)
*Date*		*Day 1*		*Day 35*	*Day 185*
Protocol explanation	✓				
Oral consent		✓			
Randomization		✓			
K-SADS parents		✓			
K-SADS children		✓			
Socio-demographic questionnaire		✓			
PCL-5		✓		✓	✓
LEC-5		✓			
CPC child version		✓		✓	✓
CPC parent version		✓		✓	✓
CYRM child version		✓		✓	✓
CYRM parent version		✓		✓	✓
MFQ child version			Session 2 of the CFTSI group		
MFQ parent version			Session 1 of the CFTSI group		
PTSD-RI child version			Session 2 of the CFTSI group		
PTSD-RI parent version			Session 1 of the CFTSI group		
Family booklet			Sessions 3, 4, and 5 of the CFTSI group		
MFQ common version			Sessions 4 and 5 of the CFTSI groupCFTSI		
PTSD-RI common version			Sessions 4 and 5 of the CFTSI group CFTSI		
Developmental history			Session 1 of the CFTSI group		
THQ adapted adult and parent version			Session 1 of the CFTSI group		
THQ adapted child version			Session 2 of the CFTSI		
PCL-C *PCL-5 adapted to CFTSI			Session 1 of the CFTSI group		
Satisfaction questionnaire			Session 5 of the CFTSI group		

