### Statistical methods

The statistical analyses will be detailed in a statistical analysis plan (SAP) finalized before the last patient in the study is included.

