#### Analysis of primary endpoint

The analysis of the primary endpoint will be performed on an intention-to-treat basis. The primary endpoint (pre-post intervention variation in the child version of the CPC score) will be compared between the two groups using an analysis of covariance (ANCOVA) in order to adjust for the stratification criteria of the randomization. The effect size will be determined using Cohen’s d.

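### The primary time point is end of programme (T1) in Trial design but 3 months later (T2) in the abstract and the primary aim

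*Protocol article*

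**What the plan says.** All places are in the protocol article.

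- **Trial design** defines the two follow-up assessments as "immediately after completion of the program (T1), and 3 months after completion of the program (T2"), and then states "The primary outcome point is set as T1".
- **Abstract, Methods** has the primary outcome "assessed using the Child Posttraumatic Stress Checklist 3 months after completion of the program", which is T2. The same paragraph goes on: "Secondary outcomes include three-month symptom persistence, parental PTSD symptoms, and predictors of response".
- **Aims of the study, primary aim** is the effect on the CPC "at 3 months after completion of the program, in children and adolescents aged 7 to 17", again T2.
- **Aims of the study, first secondary aim** is the effect on symptoms "in children and adolescents on the CPC, at 3 months after completion of the program", against the same comparator.
- **Primary outcome** gives baseline, T1 and T2 as the time frame and singles out none.
- **Analysis of primary endpoint** reads "The primary endpoint (pre-post intervention variation in the child version of the CPC score"). This fits T1 but does not name it.
- **Sample size** uses a standardised effect of 0.53 with no time point attached.
- **Statistical methods** says that the SAP will be "finalized before the last patient in the study is included".

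**The concern.** The effect at the end of the programme and the effect 3 months later are different questions. The Background notes that some children recover spontaneously, and by T2 there has been more time both for that recovery and for drop-out. A benefit could be present at T1 and gone at T2, or emerge only at T2.

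As written, either result could later be presented as the pre-specified primary with a supporting citation from the article. The 5% error rate is then unprotected for as long as the choice stays open. The SAP is a weak safeguard, because it may be finalised when much of the outcome data already exists.

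**Working it through.** **1. The statements side by side**

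| Section | Time point for the child CPC | Role |
|---|---|---|
| Trial design | T1, named | primary |
| Abstract, Methods | 3 months (T2) | primary |
| Abstract, Objective and Methods | 3-month persistence | secondary |
| Primary aim | 3 months (T2) | primary |
| First secondary aim | 3 months (T2) | secondary |
| Primary outcome | baseline, T1 and T2 | none chosen |
| Analysis of primary endpoint | pre to post, T1 implied | primary |
| Secondary outcomes; secondary endpoint 1 | baseline, T1 and T2 | secondary |

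One statement names T1 as primary and two name T2. The 3-month comparison is both primary and secondary. No passage reconciles these or declares co-primary time points.

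**2. Does the sample size settle it?**

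Inputs from Sample size: effect 0.53, two-sided 5%, power 80%, drop-out about 20%.

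- Normal approximation: n = 2 × (1.960 + 0.842)² / 0.53² = 55.9, so 56 per group.
- Two-sample t-test (noncentral t): 56.86, so 57 per group, which is the stated figure.
- Drop-out: 56 / 0.8 = 70 and 57 / 0.8 = 71.25, so 72. The stated 70 per group is close to both.

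The calculation therefore sizes one primary comparison. It does not show which.

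**3. False-positive rate if either time point can serve as primary**

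Take the two test statistics as bivariate normal with mean 0 and correlation r, each tested at |z| > 1.96. The error rate is 1 − P(|z₁| ≤ 1.96 and |z₂| ≤ 1.96). The document does not give r, so a range is shown. Independence, 1 − 0.95² = 9.75%, is the reference case.

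**4. How often the label decides the verdict**

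Assume that 0.53 holds at both T1 and T2, with 70 × 0.8 = 56 analysed per arm. The mean of each z is 0.53 × √(56/2) = 2.80, which gives 80% power for each test alone. The chance that exactly one is significant is 2 × [P(one given test not significant) − P(neither significant)].

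| Assumed r | At least one false positive | Exactly one significant at the planned effect |
|---|---|---|
| 0.5 | 9.1% | 22.5% |
| 0.6 | 8.8% | 20.1% |
| 0.7 | 8.3% | 17.4% |
| 0.8 | 7.8% | 14.2% |

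**5. How much data could exist when the SAP is finalised**

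Study setting has recruitment from December 2025 to June 2027, about 18 months or 78 weeks. By the Outcomes section, T1 falls at most about 2 + 8 = 10 weeks after T0, and T2 falls 12 weeks later, at 22 weeks. With even accrual (an assumption), the share of participants past each assessment at the last inclusion is:

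- T1: 1 − 10/78 = 87%
- T2: 1 − 22/78 = 72%

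**The case against.** The strongest reply is that this is a drafting slip and not a plan with two primary endpoints. The trial is sized for one comparison, and no text plans two primary tests. The abstract treats 3-month persistence as secondary, and the first secondary aim makes sense only if the primary aim was meant for T1. That reading is plausible, but it remains an inference. The secondary CPC endpoint also covers T1, and the two 3-month statements stand in the abstract and the primary aim, where a reader looks first.

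Three further points stand as limits:

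- The error rates apply only if the more favourable time point is picked. The protocol contains no such rule, so the figures illustrate what an open choice would cost. The 14% to 23% also needs the same effect at both times, which the document does not claim.
- Data existing is not the same as comparative results being known. The study is described as open-label, but the outcome assessors are blinded, and the database is frozen only after verification.
- The registry record and the full protocol are not shown and may already fix the time point.

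None of this removes the contradiction. A condensed article can omit detail, but condensing does not explain opposite statements about the primary time point. The choice is not simply left to the SAP either, because the article fixes it in two incompatible ways.

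**Conclusion.** The concern holds. The article gives two incompatible primary time points for the same measure, so the primary analysis cannot be carried out as written without someone choosing between them.

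While that choice is open, the nominal 5% could become 7.8% to 9.1%. At the planned effect, between about one trial in seven and one in four would have a verdict that depends on the choice. These figures rest on an assumed correlation of 0.8 to 0.5, and the second also on an equal effect at both times. The contradiction itself needs no assumption. It must be corrected, because it concerns which result decides the trial.

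**What to change.** Name one primary time point and state it identically in the abstract, the primary aim, Trial design, the Primary outcome time frame, Analysis of primary endpoint and the registry entry.

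- **If T1 is intended**, as the layout of the secondary objectives suggests: change the abstract and the primary aim to T1, write T1 into the primary analysis, and keep 3 months as the first secondary aim.
- **If T2 is intended**: change Trial design and the primary analysis to T2, change the duplicated secondary aim to T1, and stop listing 3-month symptoms as secondary.

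In either case, state that the 0.53 effect and the 20% drop-out refer to the chosen time point. If they do, the sample size is unchanged. Keeping both as primary at two-sided 2.5% each would instead need 69 per group before drop-out, and 69 / 0.8 = 86.25, so 87 per group or 174 in total.

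The cost is a wording amendment. It should be made before the first inclusion and not left to the SAP. Recruitment was due to begin in December 2025, soon after publication in November 2025. If it has already begun, a dated amendment made before anyone sees outcome data by arm is the fallback.
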